Initial pilot results [20] indicated that completion of the SUM alone was associated with statistically significant decreases in the odds of drug use (*B* = − 3.62; *p* = .03) and drug use related problems as measured by the Drug Abuse Screening Test (DAST-10) [17] (*B* = − 0.75; *p* = .02) at 1-month post-intervention. While CT videos were not independently associated with reductions in drug use or DAST-10 scores; they significantly enhanced the long-term benefits of SUM completion. At 3-month and 6-month follow-up the SUM was only associated with significant decreases in the odds of drug use (*B* = − 2.79; *p* = .013 and *B* = − 3.93; *p* = .014 respectively) and DAST-10 scores (*B* = − 0.64; *p* = .01 and *B* = − 0.79; *p* = .003 respectively) among men who viewed the CT videos. In a direct comparison between the CHTC as usual condition and those participants who received both *We Test* adjunct components (CHTC+SUM+CT video), the combined condition had significantly lower odds of drug use at 1- and 3-month follow up and significantly lower DAST-10 scores at all follow-up time-points.

While promising, the results of [name] et al. [20] were limited in several ways. First, their study did not include biological markers for drug use and sexual risk taking to validate self-report responses. Second, the most distal follow-up was 6-months post-intervention. This was not sufficiently long enough to observe decay in the treatment effect for substance use outcomes. This limited the development of guidance or recommendations on the timing of CHTC-retesting with *We Test* module delivery. The next step in this program of research is to conduct a full scale efficacy trial that incorporates the use of biological markers in addition to self-reported behavioral data and a more extensive follow-up period with an expanded potential to observe decay in the intervention effect.

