### Objectives

The purpose of the current study is to evaluate the efficacy of CT and SUM adjunct modules that augment the existing CHTC protocol. Our primary hypotheses are that completion of the SUM will be associated with a statistically significant decrease in drug use and drug-related problems at all follow-ups. We also hypothesize that viewing CT videos will enhance the effect of SUM. Based upon our initial results, we anticipate that there will not be a direct effect of adjunct intervention components on HIV Transmission Risk Behavior (TRB); however, we have powered the study to examine indirect effects. We therefore propose secondary hypotheses in which the SUM and CT components significantly reduce sexual HIV transmission risk behavior as a result of decreases in drug use.

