## Methods

### Trial design

This study utilizes a randomized controlled trial design to evaluate the efficacy of two adjunct intervention components for couples HIV testing and counseling (CHTC). Participants are randomized in a full-factorial design to one of 4 conditions: CHTC as usual; CHTC + CT videos; CHTC + SUM; or CHTC plus both adjunct components.

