#### Sample size

Power analyses were generated by Monte Carlo simulation using Mplus (version 8.0). All estimates were based upon 10,000 sample replications and power was defined as the percentage of randomly generated samples in which the specified parameter was statistically significant. All simulated models were multi-level, nesting participants (at Level 1) within couples (at Level 2). Models focused on detecting between-condition differences at any one follow-up time-point (as opposed to predicting slope factors). This allowed for more direct extrapolation of error variances from existing baseline data and is consistent with the primary aim of the study. The main effects of the two interventions (the drug use calendar and video-based communication skills training) as well as their interaction were modeled at level 2. Based upon the results of our previous studies, we anticipate 80% minimum follow-up retention at 12 months. These analyses therefore reflect a conservative analytic sample of 240 couples (480 individuals).

Analyses indicated that the proposed study has power > .80 to detect a simple main effect of SUM and/or CT videos corresponding to a 15% reduction in the odds of drug use and a 1.0 point reduction in DAST scores at any follow-up time point. The proposed study has power > .80 to detect a 2% reduction in the odds of reporting HIV TRB. Effects of these magnitudes are plausible given our pilot data. *We Test* pilot data have indicated that mediational pathways linking CT videos with drug use outcomes likely involve depression. The effects of viewing ACTV were generally small across indices of communication skills and psychological functioning. The most promising (statistically significant) effects were associated with improvements in self- disclosure communication (β = .13) and depression (β = −.16). Notably, the indirect pathway between CT and depression through self-disclosure communication was of moderate size (β = −.12) indicating that communication skills may be one mechanism by which ACTV yields reductions in depression. Depression scores were, in turn, positively associated with the odds of drug use (β = −.45) and DAST scores (β = .06). Using these effects as preliminary estimates, Monte Carlo simulations suggested that the proposed study design has power > .80 to detect the significance of direct pathways and implied indirect effects of intervention.

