#### Primary analyses of intervention effects

Outcome variables will be tested by applying a multilevel latent growth model to follow-up data, accounting for nesting within couples. Models will utilize 5 data points (Baseline, 3-, 6-, 9-, and 12-month follow up) and full-information maximum likelihood estimation to ensure that all randomized participants are included in analyses – consistent with the ITT paradigm. Models will include an intercept (representing the initial outcome value) and two slope factors. The first slope-coefficient will quantify change from baseline to post-intervention. The second will capture change over time post intervention. Mplus accommodates count and dichotomous outcomes. Growth factors will then be regressed on intervention condition at the couple level (Level II) and the effect of the intervention will be evaluated by examining the regression coefficient (and associated *p* value) associated with intervention condition for each of these factors.

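### The efficacy tests named in the primary analysis (condition on an intercept and two slopes) are not the follow-up-specific SUM effects or the SUM-by-CT interaction that the plan hypothesises, nor the contrasts it powers

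*Protocol article*

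**What the plan says.** Three sections of the protocol article bear on this.

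- **Objectives.** The primary hypotheses are that "completion of the SUM will be associated with a statistically significant decrease in drug use and drug-related problems at all follow-ups". The next sentence adds: "We also hypothesize that viewing CT videos will enhance the effect of SUM". The first is a claim about each of the visits at 3, 6, 9 and 12 months. The second is an interaction between the two factors.
- **Sample size.** The simulation is described this way: "Models focused on detecting between-condition differences at any one follow-up time-point (as opposed to predicting slope factors". The two component main effects "as well as their interaction were modeled at level 2". The section calls this choice consistent with the primary aim, and it gives power above .80 for a simple main effect of SUM and/or CT at any follow-up.
- **Primary analyses of intervention effects.** Five data points are modelled with an intercept (the initial outcome value), a slope from baseline to post-intervention and a slope over time thereafter. Then: "Growth factors will then be regressed on intervention condition at the couple level (Level II) and the effect of the intervention will be evaluated" by the regression coefficient and p value for intervention condition on each of these factors.

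The Background explains why the interaction matters. In the pilot, CT videos had no independent effect on drug use, but "they significantly enhanced the long-term benefits of SUM completion". The later pilot result is put this way: "At 3-month and 6-month follow-up the SUM was only associated with significant decreases in the odds of drug use", and it is restricted to men who had viewed the videos.

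**The concern.** The sample size section sets slope factors aside as the target of the power work, and the primary analysis then makes slope factors the target of inference. The article therefore fixes a decision quantity that differs from both the hypothesis and the power statement.

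Two things are at stake. First, the p values the plan names do not answer whether SUM works at all follow-ups or whether CT enhances it. With three condition coefficients per outcome and no stated link to the hypotheses, what counts as success could be settled after the results are seen. Second, the stated power could be read as applying to the slope coefficients or to the interaction, for which the article gives no figure.

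**Working it through.** **1. The plan's own figure.** Power above .80 cannot be reproduced, because the article gives no alpha, base rate, SD or within-couple correlation. The point below does not depend on whether that figure is right, only on which quantity it describes.

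**2. What each coefficient measures.** The article gives no intermediate assessment before 3 months, so take the first slope to end there (an assumption). The loadings at baseline, 3, 6, 9 and 12 months are (1,0,0), (1,1,0), (1,1,1), (1,1,2), (1,1,3). Let D1 and D2 be the between-group differences in the first and second slope. The effect at follow-up k (k = 0, 1, 2, 3), as a difference in change from baseline, is D1 + k x D2:

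- 3 months: D1
- 6 months: D1 + D2
- 9 months: D1 + 2 x D2
- 12 months: D1 + 3 x D2

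Only the first of these is a single coefficient. The intercept is the pre-randomisation value, so a condition difference there is chance imbalance and not efficacy.

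**3. What the named tests can show.** Inputs: 240 couples, 480 individuals (Sample size), so 240 individuals per level of SUM if allocation is equal. Assumed: within-couple correlation 0.3, compound symmetry with repeated-measures correlation r = 0.4, two-sided 0.05, standardised continuous outcome.

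- Effective n per level = 240/1.3 = 184.6.
- Var(D1 + k x D2) = (2/n)(1 - r)[1 + 1/4 + (k - 1.5)²/5].
- k = 0 or 3: 0.01083 x 0.6 x 1.70 = 0.01105, SE 0.105.
- k = 1 or 2: 0.01083 x 0.6 x 1.30 = 0.00845, SE 0.092.
- Var(D2) = 0.01083 x 0.6/5 = 0.0013, SE 0.036.
- Power = Φ(|effect|/SE - 1.96).

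| Pattern | D1, D2 | Power D1 | Power D2 | Power at 3, 6, 9, 12 months |
|---|---|---|---|---|
| Sustained | -0.30, 0 | 0.81 | 0.03 | 0.81, 0.90, 0.90, 0.81 |
| Fades to half | -0.30, 0.05 | 0.81 | 0.28 | 0.81, 0.78, 0.59, 0.30 |
| Fades to zero at 12 months | -0.30, 0.10 | 0.81 | 0.79 | 0.81, 0.59, 0.19, 0.03 |

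The 0.03 entries are the one-sided error rate of 0.025 where the true value is zero. With r = 0.6, the fade-to-zero row becomes 0.94 for D1 and 0.94, 0.76, 0.27, 0.03 for the visits. The first slope thus behaves identically in three situations in which the hypothesis of an effect at all follow-ups has different answers.

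**4. First slope against the powered quantity.** Take a single-follow-up contrast with 80% power (z = 2.80). Relative variances, in units of σ² and for r = 0.3 and 0.5: first slope (1 - r) x 1.70 = 1.19 and 0.85; unadjusted single visit 1; baseline-adjusted single visit 1 - r² = 0.91 and 0.75.

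- Against the unadjusted visit: Φ(2.80/√1.19 - 1.96) = 0.73; Φ(2.80/√0.85 - 1.96) = 0.86.
- Against the adjusted visit: Φ(2.80 x √(0.91/1.19) - 1.96) = 0.69; Φ(2.80 x √(0.75/0.85) - 1.96) = 0.75.

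First-slope power is therefore about 69% to 86% where the powered contrast has 80%: a different number, but not a collapse.

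**5. The interaction.** With four equal cells and cell-mean variance v, a factor main effect has variance v and the difference of differences has variance 4v. Main-effect power therefore does not carry over to SUM x CT. The moderators listed under Moderation/mediation analyses (demographics, socioeconomic status, HIV status, agreements, relationship variables) do not include CT as a moderator of SUM, so the interaction is not picked up there.

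**The case against.** The other side has four good arguments.

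- **Intervention condition is probably shorthand.** A reader might infer that the four arms enter as one score that cannot separate SUM from CT. The article does not say so. The sample size section also speaks of between-condition differences before listing two main effects and an interaction, and Trial design states: "Participants are randomized in a full-factorial design to one of 4 conditions". Factorial coding at the couple level is the natural reading. This stands: the fault is that the interaction is not named as a test, not that the model excludes it.
- **The hypotheses are not untestable.** A reader might infer that the model can neither confirm nor refute them. That is too strong. Every follow-up effect is a linear function of the two fitted slopes, and the article already mentions model constraints, though for indirect effects. A lasting benefit should show as a non-zero first slope with a second-slope difference near zero. This stands only in part: a non-significant second slope is not evidence of persistence. In the fade-to-half row, D2 has power 0.28, so the same pattern of p values would often appear.
- **The simplification is disclosed.** The sample size section says that it targets single visits and why (error variances could be taken from baseline data). That justifies the simulation, but it does not make its result apply to slope tests.
- **Any power loss is modest.** A reader might infer a large loss from using slopes. Against the contrast the plan actually powers, step 4 shows a small loss or, at r = 0.5 unadjusted, a gain. Low interaction power is a property of any 2 x 2 trial of this size and is not caused by the growth model.

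Full model code can be left to an analysis plan. The decision quantity, however, is stated in the article, and it does not match the Objectives.

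**Conclusion.** The point holds as a mismatch between stated tests, hypotheses and power. The intercept coefficient carries no efficacy information. The first slope reflects at most the 3-month effect. A sustained benefit gives a zero second-slope difference, and a fading benefit can give a significant first slope although nothing remains at 12 months (0.81 on the first slope against 0.59 and 0.19 at 6 and 9 months in the illustration). No test is named at 6, 9 or 12 months or for SUM x CT. The power above .80 belongs to single-visit main-effect contrasts.

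The structural finding needs only the loadings and the assumption that the first slope ends at 3 months. The power figures also rest on assumed correlations, an assumed effect size, equal allocation and a continuous-outcome approximation. Drug use and transmission risk behaviour are dichotomous, so those figures are illustrative. The documents do not support the claims that the trial cannot test its hypotheses, that the arms are scored as one variable, or that power is severely reduced.

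**What to change.** Reconcile Objectives, Sample size and Primary analyses of intervention effects:

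1. Regress the growth factors on SUM, CT and SUM x CT at the couple level and state the coding (for example ±1/2, so that the SUM coefficient is averaged over CT).
2. State that the intercept coefficient is not an efficacy test.
3. Make the SUM contrasts at 3, 6, 9 and 12 months the primary evaluation, either as first slope + k x second slope (k = 0 to 3) by model constraint or with visit as a categorical factor. An average over the four follow-ups may be added, but it is optional and does not by itself answer a hypothesis about all follow-ups.
4. Name the SUM x CT contrast as the test of CT enhancement.
5. Keep the second slope as a description of decay.
6. State that the power above .80 applies to the single-time-point main-effect contrasts, not to the slope coefficients or the interaction.

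The cost is analysis wording and a few lines of model code. No new data, visits or participants are needed.

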#### Moderation/mediation analyses

We will conduct analyses to identify putative moderators and mediators of intervention effects. Moderation analyses will focus on demographic factors that have been linked to HIV disparities. Specifically, we will examine whether the effect of the intervention is constant across race and ethnicity, age, and indicators of socioeconomic status (income and education) in all proposed analyses. We will also examine whether intervention effects vary across couples’ HIV status, incorporating attention to viral suppression and PrEP uptake.

We utilize the actor–partner interdependence model (APIM) Kenny et al. [6] to organize individual-level mediators. APIMs are multilevel models. At the individual level (Level 1), there are two types of effects: *actor* (the association between an individual’s score on an outcome and his own score on a predictor) and *partner* (the association between an individual’s score on an outcome and his partner’s score on a predictor). Couple-level (Level 2) effects are calculated for variables where both partners share a score (e.g., relationship length).

A series of APIMs will be calculated to examine putative mediators. Due to model complexity, each drug and TRB outcome will be examined separately. As with primary outcome analyses described above, we will utilize growth modeling procedures to calculate an intercept and slope for each outcome over time. Similarly, models will also specify growth factors for mediators at Level 1 and Level 2 during the follow-up period. In this manner, growth factors for the outcome can be regressed on growth factors for the putative mediator at both Level 1 and Level 2. Subsequently, the effect of intervention (a couple-level predictor) will be determined by examining the regression coefficients associated with intervention in the prediction of growth factors for both the outcome of interest and the mediator at Level 2. Where indicated by the pattern of significant direct effects, indirect pathways from intervention condition through actor and partner effects of the mediator will be tested using bootstrapping tests of mediation. Where outcome distributions prevent the use of bootstrapping, we will utilize a model constraint approach to evaluating the significance of indirect effects.

Follow-up exploratory analysis will investigate a range of potential mediators and moderators. In particular, we will test whether drug use mediates intervention effects on sexual risk taking outcomes. In addition, individual variables assessing mental health, discrimination, perceptions of relationship functioning, and communication skills will be tested as potential mediators of intervention condition effects. Meanwhile, baseline differences in agreements, agreement satisfaction, relationship satisfaction, commitment, and decision-making power will be tested as potential moderators of intervention effects.

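### The indirect effect on TRB through drug use is a powered secondary hypothesis in the Objectives, but the analysis plan calls it exploratory and puts an undefined significance gate in front of it

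*Protocol article*

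**What the plan says.** Three parts of the protocol article bear on one test: whether SUM and CT lower TRB by lowering drug use.

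- **Objectives.** No direct effect of the components on TRB is anticipated, but "we have powered the study to examine indirect effects". The authors then set out "secondary hypotheses in which the SUM and CT components significantly reduce sexual HIV transmission risk behavior as a result of decreases in drug use".
- **Moderation/mediation analyses, procedure.** Actor–partner models are fitted to putative mediators, and "each drug and TRB outcome will be examined separately". The intervention effect is judged from the "regression coefficients associated with intervention in the prediction of growth factors for both the outcome of interest and the mediator at Level 2". The next sentence sets the condition: "Where indicated by the pattern of significant direct effects, indirect pathways from intervention condition" are tested, by bootstrap or by a model constraint.
- **Moderation/mediation analyses, closing paragraph.** Under follow-up exploratory analysis stands: "In particular, we will test whether drug use mediates intervention effects on sexual risk taking outcomes".

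Two further places matter. Primary outcomes lists TRB beside illicit drug use. Sample size claims power above .80 for direct pathways and the indirect effects they imply.

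**The concern.** A test cannot be both a powered, named hypothesis and one item in an exploratory list. The label decides how a positive result may be reported. TRB is listed as a primary outcome, and the indirect route is the only one by which the authors expect the components to change it.

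The gate is the second difficulty. An indirect effect can exist when neither the total effect nor the remaining direct effect of intervention on the outcome is significant. A rule that needs a significant intervention effect on TRB therefore does not suit a hypothesis whose authors expect no direct effect there. The text does not say outright that this effect is needed, but two things point that way. The Objectives use the term direct effect for intervention on TRB, and the sentence just before the gate names the intervention coefficient on the outcome as well as the one on the mediator.

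**Working it through.** **The plan's own figures.** The analytic sample is consistent: 240 couples × 2 = 480 individuals, and at 80% retention 240 / 0.80 = 300 couples randomised. The power above .80 for indirect effects cannot be reproduced for this hypothesis. The path coefficients reported under Sample size run from CT through self-disclosure and depression to drug use and DAST scores. No drug-use-to-TRB path, TRB base rate, within-couple correlation or significance level is given.

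**Reading the text.**

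| Question | Objectives | Mediation procedure | Closing paragraph |
|---|---|---|---|
| Status of the test | Secondary hypothesis | Not stated | Exploratory |
| Conditional on significance? | No condition given | Yes, on direct effects | No |
| Procedure | None | Bootstrap or model constraint | None |

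If the closing paragraph borrows the procedure above it, the test is gated. If it does not, the test is ungated but exploratory and has no stated method. Either way it does not match the Objectives.

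**How much the gate matters.** This is an illustration; every input except the 240 couples is assumed. It uses a linear couple-level model with balanced intervention X coded ±1, mediator M = aX + error and outcome Y = bM + error. M has variance 1, the error variance of Y is 1 − b², and there is no residual direct effect. A path counts as significant if |t| > 1.97 (two-sided 5%). There were 4,000 replicates per setting. Each cell is the share of trials in which the indirect test is reached.

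| a / b | a and b significant | also total X→Y significant | also residual direct X→Y significant |
|---|---|---|---|
| 0.20 / 0.20 | 75.8% | 7.0% | 3.6% |
| 0.20 / 0.30 | 87.5% | 14.8% | 4.3% |
| 0.25 / 0.25 | 94.9% | 15.2% | 4.8% |
| 0.30 / 0.30 | 99.6% | 27.4% | 5.0% |
| 0.30 / 0.45 | 99.8% | 54.8% | 4.9% |

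**Check by formula, a = b = 0.20.** Expected t for each path:

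- a: 0.20 × √240 / √(1 − 0.04) = 3.16, so power P(Z > 1.97 − 3.16) ≈ 0.88.
- b: 0.20 × √240 × √(1 − 0.04) / √(1 − 0.04) = 3.10, power ≈ 0.87.
- Both: 0.88 × 0.87 ≈ 0.77, against 0.758 simulated.
- Total effect: 0.20 × 0.20 × √240 = 0.62, power ≈ 0.09, against 0.093 simulated for the total effect alone.

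The total effect is the product of two paths, so it is much smaller than either of them. That is why a gate on the total effect fails when mediation is present. A gate on the residual direct effect opens at about the 5% error rate, because in this model that effect is zero.

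**The case against.** **The test is promised without condition.** The closing paragraph says drug use will be tested as a mediator of effects on sexual risk outcomes. A reader might infer from the gate alone that the hypothesis may never be tested; the article does not support that. What stands is that the promise sits under the exploratory label, brings no procedure, and conflicts with the gated procedure above it.

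**Direct effects may mean component paths.** In path modelling any single arrow can be called a direct effect, and Sample size speaks of direct pathways that imply indirect effects. On that reading a null intervention effect on TRB blocks nothing. This is a fair reading, and it narrows the finding. It does not settle it: the article uses the term both ways, and even here it does not say which growth factors, levels, or actor or partner paths must be significant.

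**The loss is not one number.** A reader might reason that a null direct effect opens a 5% gate, so the hypothesis goes untested 95% of the time. That holds only for one coefficient and one reading. With several growth factors, two components and their interaction, and three TRB indicators, the chance that some gate opens is higher. If mediation exists, the total effect is also not zero.

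**Temporal order.** One might go further and require earlier drug use to predict later TRB. The article does not justify prescribing that. Its background cites a day-level link between drug use and condomless sex, which widely separated visits could miss. The primary model already has two ordered slopes, and the urine assay and the chlamydia or gonorrhea result do not come from the same interview calendar. At most, growth factors over the same follow-up period limit what can be said about causal direction.

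**Conclusion.** The concern holds as an inconsistency in the text. The Objectives, the mediation procedure and the closing exploratory paragraph disagree on whether this test is secondary or exploratory, and on whether it depends on significance elsewhere.

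The consequence depends on the reading. If the intervention effect on TRB is part of the gate, the test is reached in about 4–27% of trials for assumed paths of 0.2 to 0.3. The total-effect version rises to about 55% at the strongest setting tried (0.30 / 0.45). If only the component paths count, it is reached in 76–100%, and the loss is small. These figures rest on assumed path sizes, an assumed 5% level, a linear outcome and no residual direct effect. The TRB indicators are dichotomous and the planned model is more complex, so the figures show the direction and rough size of the problem and are not a forecast for this trial. The inconsistency itself needs no calculation.

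This should be corrected, because it bears on what the trial may conclude about TRB.

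**What to change.** In the moderation/mediation section:

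1. State that the indirect effect of SUM (and SUM × CT) on TRB through drug use is a prespecified secondary analysis, in line with the Objectives.
2. State that it is estimated and reported with its confidence interval whatever the significance of the intervention effect on TRB.
3. Move it out of the exploratory paragraph and leave the other mediators there. If a gate is kept for those, say which paths it refers to.
4. Optionally, add that mediator and outcome growth factors over the same period limit inference about causal direction.

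The cost is a few sentences and matching analysis code. No data collection, visit or sample size changes.

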#### HIV transmission risk behavior (TRB)

Primary Analyses focus on three dichotomous behavioral indicators of TRB These include: (1) Condomless anal sex (CAS) with a casual partner in the absence of PrEP; (2) CAS with a sero-discordant main partner (whose viral load is detectible) or concurrent CAS between main and casual partners in the absence of PrEP; (3) Any chlamydia or gonorrhea diagnosis in the absence of PrEP.

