### Data analysis plan

#### Data screening procedures and analyses of attrition

We will follow standard procedures in cleaning data and examining distributional properties (means, standard deviations, skew, kurtosis, and visual representations). Subsequently, we will conduct an analysis of attrition to determine if dropout is associated with 1) demographic variables and/or 2) drug use or TRB outcomes assessed at baseline. Factors which are observed to covary significantly with attrition will be incorporated in outcome analyses. [name] (Co-I) is an accomplished epidemiologist who is familiar with modeling procedures applicable to the modeling of variables with non-normal distributions (i.e., categorical and count variables), and we will utilize appropriate tests of association and linking functions in statistical models. [name] will utilize Mplus (version 8.0) [12] in conducting these analyses.

Analyses will utilize a true intent-to-treat procedure involving data from all randomized couples. Mplus has a variety of options for handling partial attrition including full-information maximum likelihood estimation. Non-random and consequential missingness can also be modeled directly through the addition of latent variables which account for the probability of missingness at any time point.

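### The fallback test for indirect effects, on its usual reading, is conservative and could cost the secondary hypotheses between almost nothing and about 21 points of power; a Monte Carlo interval would avoid most of that loss

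*Protocol article*

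**What the plan says.** The Objectives section of the protocol article expects no direct effect of the adjunct components on TRB. It makes the indirect route, with drug use as the mediator, the secondary hypotheses: "We therefore propose secondary hypotheses in which the SUM and CT components significantly reduce sexual HIV transmission risk behavior as a result of decreases in" (the sentence ends by naming that mediator). It adds that "we have powered the study to examine indirect effects".

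The outcome section on TRB states that "Primary Analyses focus on three dichotomous behavioral indicators of TRB".

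Under Moderation/mediation analyses, indirect tests are run conditionally: "Where indicated by the pattern of significant direct effects". The first choice is that "indirect pathways from intervention condition through actor and partner effects of the mediator will be tested using bootstrapping tests of mediation". The fallback is: "Where outcome distributions prevent the use of bootstrapping, we will utilize a model constraint approach to evaluating the significance of indirect effects". No standard error, reference distribution or interval is named for it. The analyst "will utilize Mplus (version 8.0) [12] in conducting these analyses".

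The Sample size section claims power > .80 for direct pathways and implied indirect effects. That claim follows pilot coefficients for communication training, self-disclosure, depression and drug use or DAST scores. The section gives no coefficient for drug use on TRB and does not say which test of the indirect effect was simulated.

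**The concern.** What triggers the fallback is the distribution of the outcome. All three TRB indicators are binary, and drug use, the mediator, is itself expressed as odds of use. Both enter multilevel growth models with the intervention at couple level. It is therefore plausible that the fallback, not the bootstrap, decides the secondary hypotheses.

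On its usual reading the fallback divides the product of two path estimates by a delta-method standard error and refers the ratio to a normal distribution. The sampling distribution of a product is skewed unless at least one path is large relative to its standard error, so this symmetric test rejects too rarely. The trial could then report no mediation although both component paths are clearly supported. A less conservative interval can be computed from output the model already gives.

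**Working it through.** **The plan's own figure.** The > .80 for indirect effects cannot be reproduced. The article gives no standard errors, intraclass correlation, base rates or alpha for it, and no coefficient for drug use on TRB.

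**Inputs.**
- From the Sample size section: power > .80 for the intervention effect on drug use. At 80% power and two-sided 0.05 (assumed), the noncentrality is 1.96 + 0.84 = 2.80.
- Assumed, because no figure is given: the noncentrality zb of the path from drug use to TRB, varied from 2.8 to 10.
- Also assumed: independent, normally distributed path estimates and one product a×b.

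**Tests compared**, with both paths on the z scale:
- Delta-method Wald: reject if |ab| / √(a² + b²) > 1.96.
- Monte Carlo interval: draw both paths around their estimates, form the products, and reject if the 2.5% to 97.5% percentile interval excludes 0.

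**One case by hand.** Both paths at z = 2.5 (p = .012 each): ab = 6.25, √(6.25 + 6.25) = 3.54, ratio 1.77, p = .077. Each path is significant but the Wald test of the product is not.

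**Power**, 20,000 replicates with 2,000 draws per interval, intervention path at z = 2.80:

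| zb | Wald | Monte Carlo | Loss (points) |
|---|---|---|---|
| 2.8 | 41.0% | 61.7% | 21 |
| 3.5 | 56.2% | 73.2% | 17 |
| 4 | 65.1% | 77.5% | 12 |
| 5 | 73.7% | 80.1% | 6 |
| 6 | 76.1% | 79.9% | 4 |
| 10 | 78.8% | 80.1% | 1 |

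With both paths at 2.80, both are individually significant in 64.0% of replicates. The Wald test also rejects in only 41.0 / 64.0 = 64% of those.

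**False positives** (Wald, then Monte Carlo): both paths null, 0.0% and 0.1%; one null and the other at 2.8, 1.0% and 3.6%; one null and the other at 5, 3.0% and 4.9%. The interval gains power without exceeding 5%.

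**The pilot coefficients**, using z = β√(n − 2) / √(1 − β²) and magnitudes only:
- Communication training to depression (.16), then depression to drug use (.45). At n = 240, z ≈ 2.5 and 7.8: power 68.5% v 71.1%, a loss of about 3 points. At n = 480, z ≈ 3.5 and 11.0: 94.2% v 94.5%, essentially no loss.
- Communication training to depression (.16), then depression to DAST (.06). At n = 240, z ≈ 2.5 and 0.9, simulated at 2.5 and 1: 3.5% v 10.3%. At n = 480, z ≈ 3.5 and 1.3: 12.8% v 23.5%.

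The loss is therefore small when one path is strong and larger when neither is.

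**The case against.** The strongest objection is that the article never says delta method or Wald. A constraint only defines the product, and the full plan may fix its interval. That stands as a limit: the reading is the ordinary one for this software, but it is inferred. It does not dispose of the point, because the article names a method for judging significance and that method's ordinary form is a weak one.

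Second, this is a fallback, and nothing in the article says that binary TRB outcomes rule out the bootstrap. That is correct, so the article supports only that the fallback may well be used.

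Third, the 21-point loss belongs to an unfavourable case, and on one pilot pathway the loss is 3 points or none. This stands, and the size has to be given as a range.

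Fourth, a reader might infer that the > .80 claim does not describe the test to be used. The article does not support that. The figure follows the communication and depression pathways, not drug use to TRB. It was also simulated in Mplus and may already reflect the same conservative test. All that can be said is that the claim cannot be matched to a named test.

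Fifth, the error is in the conservative direction, and the article elsewhere lists drug use as a mediator of sexual risk under follow-up exploratory analysis. This lowers the stakes, but the Objectives section still presents it as the secondary hypotheses.

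**Conclusion.** The concern holds in a limited form. Read in the usual way, the fallback is a conservative test of a product, and it may well be applied to the secondary hypotheses. With the intervention path at 80% power, the loss against a Monte Carlo interval runs from about 21 points (second path at z = 2.8) through about 12 (z = 4) and about 6 (z = 5) to 4 or less (z = 6 and above). The article gives nothing to place the trial within that range.

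These figures rest on two-sided 0.05, independent normal path estimates and a single product. The planned models have actor and partner paths and growth factors at two levels, which would change the exact numbers. The documents do not support saying that the plan states a delta-method test, that the loss is always large, or that the > .80 figure is wrong.

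**What to change.** Replace the fallback sentence with wording such as: *Where bootstrapping cannot be used, the 95% interval for each indirect effect will be obtained by the Monte Carlo method, drawing the path coefficients from their estimated joint sampling distribution.* Drawing from the joint distribution uses the full covariance matrix, so it also covers actor and partner paths.

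In the Sample size section, state which test of the indirect effect the > .80 refers to and which pathway it covers.

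The cost is a sentence in each place and a little extra code applied to coefficients and covariances the model already outputs, with no refitting. The remaining limitation is that the interval relies on approximately normal path estimates.
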